#### Secondary outcomes

Health-related quality of life will be measured with the EuroQol (EQ-5D) [44]. This questionnaire assesses five dimensions (mobility, self-care, usual activities, pain/discomfort and anxiety/depression) on a 3-point scale (no problems, moderate problems and severe problems). This questionnaire is widely used in cost-utility analyses, and for this purpose applied in the economic evaluation as well [45,46].

Patient satisfaction will be assessed using a written 7-point NRS ranging from ‘not satisfied at all’ to ‘completely satisfied’. No gold standard is available for the measurement of patient satisfaction, but in spinal disorders a seven-point global question is recommended [33].

General health will be evaluated with the Rand-36 [47]. This questionnaire consists of 36 questions, classified in eight subscales: physical functioning, social functioning, role limitations (physical problem), role limitations (emotional problem), mental health, pain, general health perception and health change. Scores (ranging from 0-100) are transformed so that a higher score indicates a better health status. The Dutch translation of the Rand-36 has been validated as well [48].

Chronic pain experiences is measured by the Multidimensional Pain Inventory (MPI) [49]. The MPI contains 61 items divided into three parts. The first measures pain-relevant psychosocial aspects, and contains five scales. In the second part, the responses of the patient's partner to the pain (as perceived by the patient himself) are mapped out. Finally, an inventory is made of the frequency of common daily activities labelled as household chores, outdoor work, activities away from home and social activities, which together form the general activity level. The MPI (and its Dutch Language Version) is a valuable instrument for producing reliable and valid information for therapy-outcome studies with chronic pain patients [50].

#### Economic evaluation

The use of care in the pain clinics will be registered by local research nurses. They will register the type, amount and results of the diagnostic tests and treatments (interventional procedures) the patients receive. Costs of the multidisciplinary pain programme, other health care utilization, patient and family costs, and production losses will be included and relevant data collected using self-completed cost questionnaires [51]. Work absenteeism will be measured with the Productivity and Disease Questionnaire (PRODISC), which includes all relevant aspects of the relationship between health and productivity. The PRODISC was developed and validated in samples of patients and employed people in the Netherlands [52]. Costs will be valued using the guidelines published in the updated handbook for economic evaluations in the Netherlands [53]. Absenteeism from paid work will be valued using the friction cost approach [54].

An overview of the data-collection is presented in Table 1.

**Table 1 T1:** Overview of the data collection

**Outcome measures**		**Follow-up**					
	**Baseline**	**3 weeks**	**6 weeks**	**3 months**	**6 months**	**9 months**	**12 months**
**Baseline measurements**							
Demographic data	x						
Complaint history	x						
Patient expectation (CEQ)	x						
**Primary outcomes**							
Pain Intensity (NRS)	x	x	x	x	x	x	x
Global perceived recovery (NRS)		x	x	x	x	x	x
Functional Status (ODI)	x			x	x	x	x
**Secondary outcomes**							
QALY (EQ-5D)	x	x	x	x	x	x	x
Patiënt satisfaction (NRS)				x	x	x	x
General health (Rand-36)	x			x	x	x	x
Chronic pain experience (MPI)	x			x	x	x	x
**Economic evaluation**							
Costs (diaries)				x	x	x	x
Work absenteeism (PRODISC)				x	x	x	x

Abbreviations: CEQ = Credibility/Expectancy Questionnaire; NRS = Numeric Rating Scale; ODI = Oswestry Disability Index; EQ-5D = EuroQol; MPI = Multidimensional Pain Inventory; PRODISC = Productivity and Disease Questionnaire.

### Sample size

Using a power of .9, alpha .05 and a correlation of .5 for repeated measurements, a total of 85 patients per group are needed to detect a clinically relevant mean difference of two points on the NRS for pain intensity (SD 4) [55]. This difference of two points as Minimal Important Change in the NRS is based on a recent review [55]. Anticipating potential study withdrawal (20%) 102 patients per group or 204 patients per randomized comparison are needed. In total, 816 patients need to be included in the four trials.

Through an ‘educated guess’ a SD of four was chosen, because no SD can be found in the literature. Though arbitrary, it is believed conservative, and will ensure that enough patients will be included to find clinically relevant effects, if present.

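### The 20% withdrawal allowance multiplies 85 by 1.2 instead of dividing by 0.8, so 102 per group leaves fewer than the 85 the plan says it needs

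*Protocol article*

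**What the plan says.** The Sample size section of the protocol article sets out its assumptions, "Using a power of .9, alpha .05 and a correlation of .5 for repeated measurements", and a target difference of 2 points on the pain NRS with an SD of 4. From these it concludes that "a total of 85 patients per group are needed". It then adds the withdrawal allowance: "Anticipating potential study withdrawal (20%) 102 patients per group or 204 patients per randomized comparison are needed". Multiplying by four trials gives the overall target: "In total, 816 patients need to be included in the four trials".

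The section does not show the inflation formula and gives the 20% no meaning other than expected withdrawal. No other part of the article corrects or reinterprets it.

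**The concern.** An allowance for withdrawal should ensure that the required number remains after the loss. If a fraction *w* of those randomised withdraws, *N*(1 − *w*) remain, so *N* must be the required number divided by (1 − *w*). Multiplying by (1 + *w*) always gives too few, because the loss applies to the enlarged group and not to the original 85.

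The printed figures look like the second calculation. If so, the base size, the withdrawal rate and the inflated size disagree with one another. The error then passes into the size of each trial and into the overall total, and the stated 90% power does not follow from the stated withdrawal rate in any of the four trials.

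**Working it through.** **Inputs**, all from the Sample size section: difference 2, SD 4, alpha 0.05, power 0.90, 85 per group before withdrawal, withdrawal 20%, 102 per group, 204 per comparison, 816 in total. The section does not say whether the test is one- or two-sided. I assume two-sided, because that reproduces 85; a one-sided test would give 69.

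**1. The base figure reproduces.** For two means with equal groups:

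- *n* = 2 (1.96 + 1.2816)² × SD² / difference² = 2 × (3.2416)² × 16 / 4 = 84.06, which rounds up to 85.
- The t-based solution is 85.03, in line with the stated 85.
- With a correlation of 0.5, a change score has variance 2 × SD² × (1 − 0.5) = SD². A change-score comparison therefore needs the same number.

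**2. The printed 102 reproduces by multiplication.**

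- 85 × 1.20 = 102 exactly; 102 × 2 = 204; 204 × 4 = 816.

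**3. What 102 delivers under the plan's withdrawal rate.**

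- 102 × 0.80 = 81.6 remaining per group, 3.4 fewer than 85.
- 102 is enough only if withdrawal is no more than 1 − 85/102 = 16.7%.

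**4. What 20% withdrawal requires.**

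- 85 / 0.80 = 106.25, so 107 per group.
- 107 × 2 = 214 per trial; 214 × 4 = 856 in total.
- Rounding does not explain the gap: the unrounded 84.06 / 0.80 = 105.1 still exceeds 102.

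| | Printed | 85 / 0.8 | Shortfall |
|---|---|---|---|
| Per group | 102 | 107 | 5 |
| Per trial | 204 | 214 | 10 |
| Four trials | 816 | 856 | 40 (4.9% of 816) |

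**5. Effect on power.** By the normal approximation, power = Φ( (difference/SD) × √(*n*/2) − 1.96 ).

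- At *n* = 81.6: 0.5 × √40.8 = 3.194; 3.194 − 1.960 = 1.234; Φ = 0.891.
- By the noncentral t distribution at 81.6: 0.888.
- For whole numbers, 81 and 82 per group give 0.889 and 0.893 (normal), or 0.885 and 0.889 (t).
- For comparison, 85 per group gives 0.903 (normal) or 0.900 (t).

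**The case against.** The arithmetic is not open to dispute. The case against concerns how much it matters.

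- **The effect is small beside the uncertainty in the SD.** The plan says of its SD: "Through an ‘educated guess’ a SD of four was chosen". With 81.6 per group, 90% power returns if the SD is 2 × √40.8 / 3.2416 = 3.94 instead of 4, a difference of about 1.5%. This stands as a comment on size. It does not make the inflation right.
- **The analysis may be more efficient than the sample size calculation.** The Statistical analysis section plans multilevel models over time, and pain is measured at baseline and six follow-ups. Adjusting a single follow-up for baseline at correlation 0.5 would need 84.06 × (1 − 0.25) = 63.04, or 64 per group, well below 82. This partly stands: such an analysis would more than make up the loss. However, the article commits to covariate adjustment only where prognostic factors are unevenly distributed. The Sample size section also quotes the correlation and still gives 85 as the number needed, so no such gain is used to justify 102.
- **Withdrawal need not mean no data.** Patients who leave late have already given pain scores that correlate with later ones, and the planned multiple imputation can use them. Loss may also be lower at the early time points, where the Discussion expects the main effect. This stands in part: imputation can recover some of the information, but it does not fully restore outcomes that were never observed. The plan does not rely on this either, since it adds patients precisely because it expects withdrawal to cost information.

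**Conclusion.** The concern holds. The printed 102, 204 and 816 do not follow from 85 per group and 20% withdrawal; the consistent figures are 107, 214 and 856. With 102 randomised per group and 20% lost, about 82 remain and power is about 89%, roughly one percentage point below the stated 90%.

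The power figure assumes a two-sided 5% test, a difference of 2, an SD of 4, and a plain comparison of two means among patients with an observed outcome. A baseline-adjusted or repeated-measures analysis could exceed 90% with the same patients, but that is not the calculation presented. The error does not threaten the trials. It should be corrected because the planned size and power are stated wrongly for all four of them.

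**What to change.** Choose one of these in the Sample size section:

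1. **Keep 102 per group and restate the power:** with 20% withdrawal about 82 per group remain, giving about 89% power for the stated difference and SD.
2. **Keep 102 per group and restate the allowance:** 102 preserves 85 per group if withdrawal does not exceed 16.7%.
3. **Keep the claim of 90% power at 20% withdrawal:** change the figures to 107 per group, 214 per trial and 856 in total.

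The first or second is proportionate and costs one sentence, with no change to recruitment or conduct. The third costs 40 more patients over the four trials. If the primary analysis of pain is specified as adjusted for baseline, the gain at correlation 0.5 more than covers the shortfall without extra patients, and the section could then say so explicitly.

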### Treatment allocation

Patients who respond positively to the diagnostic test and give informed consent will be randomised to either a group that receives a multidisciplinary pain programme with the minimal interventional procedures, or a group receiving a multidisciplinary pain programme alone. The randomisation will be performed by a local research nurse in each of the participating pain clinics, using a computerised random number generator. The randomisation list is developed centrally. Therefore, the research nurse does not have any influence on the procedure and the treatment allocation is concealed. Randomisation will be stratified for the participating pain clinics. No treatment will be given prior to randomisation.

### Blinding

In this pragmatic trial patients and care providers cannot be blinded. Because all outcome measures are self-reported by the patient, the outcome measurement is not blinded either. Data analysis will be conducted blinded for treatment allocation and blinding will only be finished after the final analyses have been concluded. To ensure data will be analysed anonymously, all patients will be assigned a unique number. To evaluate whether lack of blinding is associated with bias, expectations and preferences of patients will be measured before randomisation and after treatment allocation. Patient satisfaction will be measured after treatment and during follow-up.

### Statistical analysis

Baseline data will be presented comparing the two treatment groups. Intention-to-treat analysis will be conducted for each follow-up moment. Missing data will be imputed with multiple imputation techniques [56,57]. The 95%-confidence intervals will be calculated for the difference of percentages (Chi-square distribution) and means (T-distribution) for dichotomous and continuous outcome variables, respectively. In case of unequal distributions of prognostic factors, multivariate analysis techniques will be used to correct for these between-group differences in prognosis. Multilevel analyses will be performed, with patient, pain clinic, and time of measurement as levels. The threshold of statistical significance is set at *p* < 0.05. Characteristics of patients with missing follow-up data will be compared to those with complete data to identify possible selective drop-out.

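### Adjusting for prognostic factors only when the randomised groups look unequal is a poor rule, and it gives up precision from baseline pain and ODI that the trial already collects

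*Protocol article*

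**What the plan says.** The Statistical analysis section of the protocol article makes three statements that bear on this.

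- Confidence intervals for differences in percentages and means come from the chi-square and t distributions, within an intention-to-treat analysis at each follow-up. No covariate is mentioned.
- Adjustment is conditional: "In case of unequal distributions of prognostic factors, multivariate analysis techniques will be used to correct for these between-group differences in prognosis". The factors are not named, and what counts as unequal is not defined.
- In addition, "Multilevel analyses will be performed, with patient, pain clinic, and time of measurement as levels". This statement carries no condition, but it names levels only and does not mention the baseline value of the outcome.

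Elsewhere, Table 1 shows pain intensity and ODI measured at baseline; global perceived recovery has no baseline value. The Treatment allocation section says: "Randomisation will be stratified for the participating pain clinics". The Sample size section assumes "a correlation of .5 for repeated measurements", a 2-point difference in pain and an SD of 4, with 85 patients per group before withdrawal.

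**The concern.** Allocation is randomised and concealed, so any baseline difference between the groups is chance. How large that difference happens to be says little about whether a covariate belongs in the model. What matters is whether the covariate predicts the outcome, and baseline pain and ODI can be expected to predict later pain and ODI. A rule keyed to imbalance therefore asks the wrong question. It leaves the covariate out in most trials, where it would still narrow the interval, and brings it in only after the baseline table has been inspected.

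Two things are at stake. One is precision, which is available at no extra data cost. The other is consistency: there are four separate randomised trials with the same primary outcomes, and the trigger could lead to an adjusted result in one and an unadjusted result in another. These results are meant to inform reimbursement and guideline decisions.

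**Working it through.** **Inputs.** From the Sample size section: difference δ = 2, SD σ = 4, alpha 0.05 (taken as two-sided, which is what reproduces the stated number), power 0.90, correlation 0.5, 85 per group, 102 after allowing for 20% withdrawal. Completers: 102 × 0.8 = 81.6, about 82 per group. *Assumptions:* the correlation ρ = 0.5 also applies between baseline and a follow-up visit, with a range of 0.3 to 0.7; the imbalance trigger is a baseline test at p < 0.05. The article gives no threshold.

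**1. The plan's own figure.** n = 2σ²(1.960 + 1.282)²/δ² = 2 × 16 × 10.507/4 = 84.06, so 85 per group. This reproduces. A change-score analysis at ρ = 0.5 has SD 4 × √(2 × (1 − 0.5)) = 4 and also gives 85. The stated number therefore takes no gain from baseline.

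**2. Always adjusting for baseline.** The variance factor is 1 − ρ² = 1 − 0.25 = 0.75.

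- Required n: 84.06 × 0.75 = 63.04, so 64 per group.
- Residual SD: 4 × √0.75 = 3.46.
- 95% half-width at n = 85: 1.96 × 4 × √(2/85) = 1.20 points unadjusted; 1.20 × √0.75 = 1.04 adjusted, 13% narrower.
- Power at 82 per arm: the standardised effect is 2/(4 × √(2/82)) = 3.20, giving about 0.89. Dividing by √0.75 gives 3.70, or about 0.96.
- Power at 85 per arm: 0.903 unadjusted, 0.964 adjusted.

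| ρ (baseline to follow-up) | Variance factor | n per group | Power at n = 85 |
|---|---|---|---|
| 0.3 | 0.91 | 77 | 0.927 |
| 0.5 | 0.75 | 64 | 0.964 |
| 0.7 | 0.51 | 43 | 0.995 |

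**3. What a trigger recovers.** Simulation of a single visit, 100,000 trials, 85 per arm, SD 4, ρ = 0.5:

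| Rule | Power (δ = 2) | Type I error |
|---|---|---|
| Never adjust | 0.900 | 0.050 |
| Adjust if baseline p < 0.05 | 0.909 | 0.044 |
| Adjust if baseline p < 0.20 | 0.924 | 0.038 |
| Always adjust | 0.962 | 0.049 |

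A separate run at 82 per arm (40,000 trials) gave power of 0.889, 0.898 and 0.956 for never, trigger at p < 0.05, and always. In that run the adjusted and unadjusted tests disagreed on significance in about 8% of trials with a true 2-point effect.

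The trigger is conservative for a simple reason. In null trials with baseline imbalance at p < 0.05, the unadjusted test rejects 18% of the time and the adjusted test 5%. The rule corrects those trials and leaves alone the remainder, in which the unadjusted test rejects less often than 5%.

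**4. Does the multilevel model already capture the gain?** Not by its levels alone. With baseline entered as an ordinary time point, the group difference in change at one visit has variance factor 2(1 − ρ) = 1 at ρ = 0.5, the same as no adjustment. For a treatment effect averaged over the six pain follow-ups, with equal correlation 0.5, the factor without baseline is (1 + 5 × 0.5)/6 = 0.58. Adjusting for baseline lowers it to 0.58 − 0.25 = 0.33. The gain remains on that estimand too.

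**The case against.** The strongest reply is that the multilevel analyses are planned unconditionally and already deal with clinic and repeated measures. This stands: only the plain intervals ignore these, and a treatment effect averaged over six visits would be more precise than a single-visit adjusted comparison even without a baseline covariate (factor 0.58 against 0.75). The single-visit power figures therefore illustrate the gain and do not forecast the plan's actual power. The reply does not remove the point, because baseline adjustment improves the averaged effect as well and the text names no baseline covariate. The full plan may add one, but it could drop the trigger only by reversing a sentence the article states.

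The inputs are also softer than they look. The 0.5 is not expressly a baseline-to-follow-up correlation, the p < 0.05 threshold is assumed, and the SD of 4 is the protocol's own guess. With an SD of 3, unadjusted power at 82 per arm would already be about 0.99. There would then be little power to gain, although the interval would still be 13% narrower at ρ = 0.5.

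Some stronger readings are tempting, and the document does not support them.

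- *The rule inflates false positives.* Applied as a fixed rule it does the opposite (about 4.4%). Type I error reaches 0.073 only if whichever of the adjusted and unadjusted results is significant may be reported. The article does not say that. Under Blinding it plans analysis blind to allocation, and the trigger looks at baseline factors, not outcomes.
- *The trial is underpowered.* Unadjusted power is about 0.90 at 85 per group and 0.89 at 82.
- *No main model or time point is named.* An article may leave that to the full protocol or analysis plan, so it is not part of this point.

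**Conclusion.** The point holds as a matter of efficiency and avoidable flexibility. The article fixes an adjustment rule that depends on chance imbalance, with unadjusted intervals otherwise, and so does not secure the precision available from baseline pain and ODI. On the plan's correlation of 0.5, read as baseline to follow-up, the loss is a quarter of the single-visit variance. The size depends on that correlation, but a gain remains across 0.3 to 0.7. An imbalance trigger recovers little of it. The figures are for pain; they carry over to ODI only if its correlation is similar, and global recovery has no baseline value of its own. This is an improvement worth making, not a flaw that defeats the trial's objective.

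**What to change.** Delete the imbalance trigger. In the multilevel model already planned, include the baseline value of the outcome as a fixed covariate for pain and ODI, and baseline pain for global perceived recovery. Keep clinic as a level. Fit this model whatever imbalance is observed, in all four trials. Report the unadjusted t and chi-square intervals as supportive results.

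The cost is a change of wording, with no new data and no extra patients. There is one small downside: if recovery is dichotomised, covariate adjustment changes what an odds ratio means. Reporting a standardised risk difference from the adjusted model avoids this and stays on the percentage-difference scale the article already uses.

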### Economic evaluation from a societal perspective

The economic evaluation will be performed according to the intention-to-treat principle and from a societal perspective. Costs of the minimal interventional procedures, physiotherapy, other health care utilization, patient and family costs, and costs of production losses will be measured and valued. Data are collected through self-completed cost questionnaires.

Missing costs and effect data will be imputed using multiple imputation according to the Multivariate Imputation by Chained Equations procedure corrected and accelerated (Bca) bootstrapping with 5000 replications will be used to estimate confidence intervals around differences in total costs between treatment groups [58,59].

A cost-effectiveness and a cost-utility analysis will be performed. Incremental cost-effectiveness ratios will be calculated by dividing the difference in mean costs by the difference in the mean effects of the two treatment groups. Using a primary clinical effect measures of the trial, for instance pain intensity. Cost-utility will be based on the EQ-5D and expressed in costs per QALY. Uncertainty surrounding incremental cost-effectiveness and cost-utility ratios will be estimated using bootstrapping techniques and graphically presented in cost-effectiveness and cost utility planes. Cost-effectiveness acceptability curves and net monetary benefit will also be estimated. Sensitivity analyses on the most important cost drivers will be performed in order to assess the robustness of the results.

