### Baseline measurement & outcomes

The core set of primary outcomes recommended for low back pain research will be used [33]. All web-based questionnaires will be assessed at baseline, three, six, nine and twelve months after the start of the treatment. Quality Adjusted Life Years (QALY), pain intensity and global perceived recovery will be assessed at three and six weeks as well.

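### The cost-utility ratio is built from differences in group means with no prespecified baseline EQ-5D adjustment, and the text and Table 1 disagree on whether costs and work absence are recorded at baseline

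*Protocol article*

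**What the plan says.** Under *Economic evaluation from a societal perspective*, incremental cost-effectiveness ratios are "calculated by dividing the difference in mean costs by the difference in the mean effects of the two treatment groups". Cost-utility uses QALYs from the EQ-5D. The section also fixes intention-to-treat, chained-equations imputation, a BCa bootstrap with 5000 replications for cost differences, bootstrapped uncertainty for the ratios, planes, acceptability curves, net monetary benefit and sensitivity analyses on cost drivers. It mentions neither baseline utility nor clinic.

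EQ-5D is taken at baseline, 3 and 6 weeks, and 3, 6, 9 and 12 months (Table 1). *Treatment allocation* stratifies randomisation by clinic. *Statistical analysis* provides multivariate correction if prognostic factors turn out unevenly distributed, and a multilevel model with clinic as a level. It does not say whether either applies to the economic evaluation.

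On timing, *Baseline measurement & outcomes* says: "All web-based questionnaires will be assessed at baseline, three, six, nine and twelve months after the start of the treatment". In Table 1, the cost row and the row that begins "Work absenteeism (PRODISC" are marked only at 3, 6, 9 and 12 months. The list of baseline content under *Baseline measurement* includes neither. *Economic evaluation* adds: "Absenteeism from paid work will be valued using the friction cost approach".

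**The concern.** Twelve-month QALYs are an area under repeated EQ-5D utilities, and a patient's later utilities are normally correlated with the first. If one arm happens to start with higher utility, part of that head start appears in its QALYs. A difference in group means keeps that part; a regression on baseline utility removes it and also narrows the interval.

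A correction triggered by observed imbalance is a weak substitute. It makes the estimator depend on the data, and it gives up the precision gain whenever the arms look balanced. The design has four separate trials, so there are four chances of a noticeable gap.

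The *Discussion* says the results are to inform reimbursement policy. A ratio with a small denominator is sensitive to small movements in that denominator.

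The second matter is data collection. Whether a patient was already absent from work at entry, and since when, is useful for valuing absence by the friction cost method. The article leaves unclear whether this is recorded, and an analysis plan written later cannot recover what was not asked.

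**Working it through.** **The plan's own figure.** *Sample size* says: "Using a power of .9, alpha .05 and a correlation of .5 for repeated measurements, a total of 85 patients per group are needed", for a 2-point difference with SD 4. Taking a two-sided test, n = 2 × (1.960 + 1.282)² × 4² / 2² = 84.06, rounded up to 85. Then 85 × 1.2 = 102, 102 × 2 = 204 and 204 × 4 = 816. All reproduce, and none is in dispute. They concern pain; no figure is given for EQ-5D, QALYs or costs.

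**Assumed inputs (not in the documents).** EQ-5D utility SD 0.15 to 0.30, the same at every visit; equal correlation r between visits of 0.3, 0.5 or 0.7; 85 evaluable per group.

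**Step 1: QALY weights.** The trapezoid rule on the Table 1 visits (0, 3/52, 6/52, 0.25, 0.5, 0.75 and 1 year) gives weights 0.029, 0.058, 0.096, 0.192, 0.250, 0.250 and 0.125. They sum to 1, and their squares sum to 0.191. The baseline visit itself carries only 2.9% of the weight, so imbalance acts mainly through correlation with later visits.

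**Step 2: chance gap at baseline.** SE = SD × √(2/85): 0.023 for SD 0.15 and 0.046 for SD 0.30.

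**Step 3: share of the gap carried into QALYs.** Slope = 0.029 + r × 0.971.

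**Step 4: precision.** SD of QALY / SD of utility = √(r + (1 − r) × 0.191). The correlation of QALY with baseline is the slope divided by this. The reduction in SE from adjustment is 1 − √(1 − correlation²).

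| r | Slope | QALY SD / utility SD | Correlation | Reduction in SE |
|---|---|---|---|---|
| 0.3 | 0.320 | 0.659 | 0.486 | 13% |
| 0.5 | 0.514 | 0.772 | 0.667 | 25% |
| 0.7 | 0.709 | 0.870 | 0.814 | 42% |

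**Step 5: shift in the unadjusted QALY difference.** Slope × SE of the gap. Smallest: 0.320 × 0.023 = 0.007. Largest: 0.709 × 0.046 = 0.033. At 1.96 SE the range is 0.014 to 0.064. The SE of the QALY difference is 0.015 to 0.040 unadjusted and 0.012 to 0.027 adjusted.

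**Step 6: what a shift does to a ratio (illustration only).** Take a cost difference of €3000, the middle of the €2500 to €3500 per treatment in the *Discussion*, as if it were the whole societal difference.

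| Assumed QALY gain | No shift | +0.02 | −0.02 |
|---|---|---|---|
| 0.05 | €60,000 | 3000/0.07 = €42,900 | 3000/0.03 = €100,000 |
| 0.10 | €30,000 | 3000/0.12 = €25,000 | 3000/0.08 = €37,500 |

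**Baseline costs and absence.** No arithmetic applies. The scheduling sentence puts every web-based questionnaire at baseline. The baseline content list and Table 1 both leave out costs and PRODISC. Two places agree with each other and one does not.

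**The case against.** **The formula is only the definition of a ratio.** A ratio of mean differences fits adjusted differences as well, the article never calls them unadjusted, and a condensed article may leave covariates to a fuller plan. It would be going too far to say that the plan commits itself to raw differences. What remains is that a section detailed enough to fix the number of bootstrap replications gives the baseline EQ-5D no role, and that the one adjustment rule in the article is conditional and sits elsewhere.

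**Randomisation protects the comparison.** This is correct. A reader might infer that any baseline gap is counted as treatment effect or that the ratio is biased. Neither follows: the unadjusted difference is unbiased on average, only about 0.3 to 0.7 of a gap carries over under these assumptions, and the bootstrap already reflects the sampling uncertainty. The loss is in precision and in the estimate conditional on the gap seen.

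**Clinic.** A reader might argue that hospital prices differ, so omitting clinic distorts costs. The article values costs from a national handbook and gives the price range only as background, so that argument fails. The case for including clinic is simply that it is the stratification factor.

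**Friction costs.** A reader might infer that absence starting before randomisation will be valued as if it began in the trial. That depends on what PRODISC asks at 3 months, and its items are not shown. The scheduling sentence may also just be loose: Table 1 has no baseline entry for perceived recovery or satisfaction either. Only the inconsistency can be established.

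**Reimbursement.** The results are meant to inform that decision; the article does not say that the ratio settles it.

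**Conclusion.** The point holds as a recommended improvement with a modest but real gain. Prespecified adjustment for baseline EQ-5D and clinic is better than differences in group means with, at most, a correction triggered by the data, and it uses only information already collected. A one-SE chance gap moves the QALY difference by roughly 0.007 to 0.033, and adjustment lowers its SE by about 13% to 42%. Both ranges rest on the assumed SD, on equal correlation between visits and, for the shift, on 85 per group. The percentage reduction does not depend on the SD or the group size. The euro figures are an illustration: they assume the QALY gain and allow for no cost offsets, which the *Discussion* considers possible.

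On baseline costs and work absence, the finding is a conflict between the scheduling sentence on one side and the baseline content list and Table 1 on the other. An error in the friction cost valuation is not shown.

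**What to change.** 1. **Economic analysis.** State that incremental QALYs and costs are estimated by regression, for example seemingly unrelated regressions, with baseline EQ-5D utility and clinic as covariates, whatever imbalance is observed. Refit the model in each bootstrap sample, and use the adjusted differences in the ratios, planes, acceptability curves and net monetary benefit. Resampling within arm-by-clinic cells is not needed: if all 13 clinics recruit to a trial, 204 / (13 × 2) is about 8 patients per cell, and naive resampling within such cells understates variance by roughly 1/8. This costs analysis wording only and needs no new data.

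2. **Baseline data.** Reconcile *Baseline measurement & outcomes* with *Baseline measurement* and Table 1, so that it is clear whether costs and PRODISC are taken at entry. If absence at entry is not recorded, add a short item on current absence and its start date to the existing web baseline questionnaire. The cost is a small extra burden for patients. It has to be done before enrolment, because it cannot be repaired at analysis.
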